### 9.1. Aims

We aim to strengthen the public’s intention and motivation to stay at home and avoid nonessential high-risk social interactions to reduce the risk of community-based SARS-CoV-2 transmission, particularly during outbreaks and new waves of confirmed cases. The primary objectives are to strategically target increasing the public’s (a) threat appraisal of COVID-19 and (b) coping appraisal of staying at home. This is expected to enhance the public’s motivation and intention to stay at home. A secondary objective is to promote psychological well-being through participatory social media activities.

### 9.2. Plan of Investigation

#### 9.2.1. Subjects

This universal public health initiative will target all HK citizens. The campaign materials will be accessible to all via the internet, and the campaign will be further promoted in outdoor and digital advertisements. Citizens aged 18 years and above may voluntarily register for the campaign to receive content updates and complete baseline and ongoing surveys.

#### 9.2.2. Methods

This 4-year project will include 6 months of preparation and content/platform creation, 36 months of intervention and 6 months of summative evaluation and report writing. A public health initiative titled “Stay Okay HK” will include the following three core components: (1) a universal health communication campaign for #StayOkayHK, (2) a consolidated Web-based platform providing ideas for home-based activities and educational resources on COVID-19 risk reduction and health promotion and (3) participatory social media strategies to engage and motivate the public to stay at home.

The #StayOkayHK communication campaign will be developed using evidence-based COVID-19 communication strategies and the principles recommended by the World Health Organization for effective communication [55]. Health communication materials will be designed in accordance with the core tenets of PMT, and will be developed with creative and marketing agencies using focus groups representative of the general public. A campaign website will house all campaign information and activities linked to social media platforms (i.e., Facebook, Instagram, YouTube). Links to the campaign website (i.e., QR code and URL) will be clearly marked on all health communication materials and advertisements. Additional health education and promotion content will be provided by leveraging resources from existing government-led health initiatives (e.g., change4health, Joyful@HK, Shall We Talk, YouthCan). Original video content on home-based activities will be developed to further enhance the public’s stay-at-home self-efficacy, and reduce perceived cost of staying at home (e.g., boredom) and rewards of participating in nonessential high-risk social activities. The online campaign platforms will be opened for Beta testing two weeks before campaign rollout. The intervention will be delivered in two consecutive phases as described below.

Phase 1: Active Campaign (12 months): In Phase 1, #StayOkayHK health communication materials will be disseminated in a territory-wide campaign via different media and advertising channels (e.g., print, digital, and social media). Targeted promotion for vulnerable groups (families with young children or elders, youths, residents of small or subdivided housing) will also be carried out via social and advertising media (e.g., paper and outdoor advertisements; distribute promotional materials at markets, transit hubs, estate offices), and through community service agencies. Original videos and social media content on stay-at-home activities will be uploaded weekly onto campaign platforms. This aligns with a life-cycle approach, which is necessary to develop and sustain an online community for health promotion [56]. The initial batch of social media posts and videos will focus on four areas. The first two foci, (1) meal preparation and (2) physical fitness, will strategically provide stay-at-home alternatives to common nonessential high-risk social interactions (i.e., dining at restaurants, working out at a gym), thereby reducing the perceived rewards for engaging in those health-compromising behaviours. Foci (3) home improvement and (4) mental wellness will aim to maximise the enjoyment of time spent at home, thereby reducing the perceived cost of staying at home. Other focal areas (e.g., preserving harmony, caring for children and elders) may be created based on user feedback. To do so, citizens registered for the campaign will be able to ‘like’ and provide feedback on the website content. They will also be encouraged to create their own social media content on home-based activities inspired by the campaign (e.g., at-home exercising) and post them on social media with the campaign hashtag ‘#StayOkayHK’.

Phase 2: Social Participation and Campaign Maintenance (24 months): In Phase 2, three sets of activities will be carried out. First, selected content created by the public and discoverable on social media platforms with the campaign hashtag will be reposted on the campaign website at the beginning of each month. Reposted content in each focal area that receives the most views/likes/shares on the campaign website at the end of each month will receive a small incentive. Second, a stay-at-home-themed social media challenge tailored to the HK context will roll out every 3 months (eight challenges in total). A random lucky draw will be conducted 3 months after each rollout and 30 participants will receive a small incentive. Third, campaign maintenance activities (e.g., targeted promotion, advertising and new videos) will take place every 6 months to sustain momentum and public participation. To keep the health communication messages up-to-date and relevant, additional health education and promotion content or relevant public health messages will also be disseminated as part of the campaign maintenance activities. Together, these activities are expected to amplify campaign reach, maintain public interest and awareness of the #StayOkayHK initiative and harness the power of the community to promote citizens’ motivation and intention to stay at home.

Study design. A repeated cross-sectional non-comparative design will be used to document campaign uptake, process and impact outcomes. A single-group pretest–posttest design will be used to assess intervention effectiveness.

Data and analysis. Ongoing analytics and campaign-focused metrics will be collected in real time on the campaign website (e.g., hits) and social media platforms (e.g., views/likes/shares). These data will be compiled and reviewed at 3-month intervals (process evaluation) and at the completion of the project (impact evaluation). Descriptive statistics will be used to present process and impact metrics on reach, adoption, implementation and maintenance. At intervention completion, a representative single-frame (mobile phone) random digit-dial telephone survey of HK adults aged 18 years and above will also be conducted to provide further evidence of campaign reach and adoption. Respondents will provide a dichotomous response (i.e., yes/no) to whether they have heard of the #StayOkHK campaign, accessed the campaign platform, perused any campaign content, and participated in any social media activities; they will also provide information on their degree of usage and satisfaction if they gave an affirmative response to the above questions. Based on the estimated adult population of Hong Kong in mid-year of 2020, a conservative estimate of 50% prevalence of exposure to the campaign, precision of 3%, and 95% confidence interval, the minimum sample size required for this telephone survey is 1068 participants.

To assess intervention effectiveness, campaign registrants will provide basic demographic information (i.e., age, sex, household characteristics, employment status, social media account, contact information) during registration (T0) and complete self-reported measures of their (a) stay-at-home motivation, intention and past-week behaviour; (b) threat and coping appraisals, measured using adapted instruments deployed in recent studies that tested PMT in the COVID-19 context [53,54]; and (c) depressive, anxiety and stress symptoms, as measured using the 21-item Depression Anxiety Stress Scale [57]. Follow-up data will be collected at the end of the active campaign (T1), and every 6 months thereafter until the end of the intervention (T2, T3, T4, T5). Invitations to complete the surveys will be delivered via the participants’ social media accounts, phone calls or email, based on the contact information provided at registration. Up to five attempts will be made before the participant is deemed lost to follow-up for that time point. To assess effectiveness, logic checking and missing data analysis will be performed. Missing data will be handled based on the degree and mechanism of missingness (i.e., deletion or imputation). Generalised estimating equations will be used to model within-subject longitudinal data to estimate population-average changes in stay-at-home motivation, intention and past-week behaviour; COVID-19 threat appraisal; stay-at-home coping appraisal; and psychological well-being (depression, anxiety, stress) across respondents over time. A minimum sample of 515 campaign registrants will be targeted to achieve 80% power and alpha of 0.0042 (to keep the overall type 1 error at 0.05 for 12 outcomes) with small intervention effect (Cohen’s d = 0.2) across timepoints for 6 repeat measures with an assumption of a first order autoregressive covariance pattern and a base correlation of 0.30.

## 10. Study 4

AI-driven Vaccine Communicator: The impact of a Web-based psychoeducation programme with a motivational AI-based digital assistant on COVID-19 vaccine hesitancy in Hong Kong’s population

To address the widespread hesitancy among HK residents toward COVID-19 vaccines, we will develop a Web-based psychoeducation programme, ‘AI-driven Vaccine Communicator,’ driven by artificial intelligence (AI) techniques based on the Vaccine Hesitancy Determinants Matrix Model and MI communication skills and concepts (theoretical underpinnings) [19].

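### Study 3 calls uncontrolled change over time among registrants intervention effectiveness, but the design cannot separate the campaign from epidemic waves and policy changes

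*Protocol article*

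**What the plan says.** All references are to the protocol article, Study 3, unless another part is named.

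- **Design (section 9.2.2, study design paragraph).** "A single-group pretest–posttest design will be used to assess intervention effectiveness". Uptake, process and impact are handled separately: "A repeated cross-sectional non-comparative design will be used to document campaign uptake, process and impact outcomes".
- **Population (section 9.2.1).** "This universal public health initiative will target all HK citizens". Adults "may voluntarily register for the campaign to receive content updates and complete baseline and ongoing surveys". These volunteers form the effectiveness sample.
- **Timing (section 9.2.2, data and analysis).** Baseline, T0, is taken when a person registers. After that, "Follow-up data will be collected at the end of the active campaign (T1), and every 6 months thereafter until the end of the intervention". With 12 months of active campaign and 24 months of maintenance, T1 to T5 fall at months 12, 18, 24, 30 and 36.
- **Analysis and power (same place).** GEE estimates population-average change in motivation, intention, behaviour, appraisals and distress. The minimum of 515 registrants is for 80% power at alpha 0.0042, a small intervention effect of d = 0.2, six measures, and a first-order autoregressive pattern with base correlation 0.30.
- **Expected background change.** The Introduction (section 1) says that people's opinions can shift with their surroundings, and that willingness to stay at home will probably fall the longer the pandemic lasts. Section 9.1 directs the campaign at staying home "particularly during outbreaks and new waves of confirmed cases".

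**The concern.** The main outcomes are motivation to stay in, perceived threat from COVID-19, coping appraisal and distress. On the document's own account, such views respond to the epidemic and its rules. With one group and no comparator, a change between T0 and a later survey is the sum of whatever the campaign did and whatever waves, restrictions and fatigue did over up to three years. The plan gives that sum the name of one of its parts.

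Baseline adds to the difficulty. Campaign materials carry the link to the website, so a person may register because an advertisement reached them. T0 may then already follow exposure, and part of any campaign effect could sit inside the baseline.

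At stake is what Study 3 can conclude. A rise in motivation during a wave could be reported as success. A fall as rules relax could be reported as failure even if the campaign slowed the decline. A larger sample or a stricter alpha does not help, because both deal with chance and this is a question of attribution.

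**Working it through.** **1. Is there a comparator anywhere in Study 3?** The campaign is territory-wide, so no unexposed group is defined. The telephone survey in section 9.2.2 runs once, at completion, and asks about awareness, access, usage and satisfaction. It does not measure the effectiveness outcomes and cannot serve as a comparison. No pre-campaign series is described, and nothing qualifies the effectiveness claim.

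**2. The plan's own figures.** Alpha: 0.05 / 12 = 0.00417, which agrees with 0.0042. Two-sided z = 2.863; z for 80% power = 0.842.

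For a one-group contrast c with correlation matrix R, and d in units of the outcome SD:

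n = c′Rc × (2.863 + 0.842)² / 0.2² ≈ c′Rc × 343

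- Adjacent times: c′Rc = 2(1 − 0.30) = 1.40, n = 481.
- T0 against T5: c′Rc = 2(1 − 0.30⁵) = 1.995, n = 685.
- T0 against the mean of T1 to T5: n = 396.

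The article does not state the contrast. The planned 515 lies inside this range, so it is neither reproduced exactly nor shown to be wrong.

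**3. How often would background change alone be declared significant?** Inputs from section 9.2.2: N = 515, alpha 0.0042, correlation 0.30 between adjacent measures. Assumptions not in the document: the size of the background shift δ, a two-sided test, complete data, and one pairwise contrast at a time.

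SE = √(2(1 − ρ) / 515)

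P(significant) = Φ(δ/SE − 2.863) + Φ(−δ/SE − 2.863)

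- T0 to T1: ρ = 0.30, SE = √(1.40/515) = 0.0521.
- T0 to T5: ρ = 0.30⁵ = 0.0024, SE = √(1.995/515) = 0.0622.

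For δ = 0.20 the first term is Φ(3.836 − 2.863) = Φ(0.973) = 0.835 for T0 to T1, and Φ(3.213 − 2.863) = Φ(0.350) = 0.637 for T0 to T5. The second term is negligible.

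| Assumed background shift, no campaign effect | T0 to T1 | T0 to T5 |
|---|---|---|
| 0.05 SD | 2.9% | 2.0% |
| 0.10 SD | 17% | 10% |
| 0.15 SD | 51% | 33% |
| 0.20 SD | 83% | 64% |
| 0.30 SD | over 99% | 97% |

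The 0.20 SD row is simply the power of each contrast for the planned effect. The test cannot tell a background shift of that size from a campaign effect of that size. A shift of the opposite sign would offset a real benefit in the same way.

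**The case against.** The design is openly declared as single-group, and a campaign aimed at everyone makes an unexposed concurrent group hard to obtain. That stands as a reason for the design. It does not justify reading the result as effectiveness.

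The illustration depends on assumed shifts, since the document gives none. That also stands: at 0.05 SD the probability is only 2–3%, and the 64–83% figure arises because the assumed shift equals the planned effect. The attribution problem does not depend on the shift chosen.

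A reader might infer more than the article supports:

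- *That the GEE uses visit labels and omits any epidemic or calendar term.* The article does not say how time enters the model or which covariates are used. A condensed article commonly leaves this to a fuller document.
- *That entry is rolling without a cutoff, so some registrants have no T1.* Registration is voluntary and T0 is at registration, but no window or closing rule is given either way.
- *That epidemic waves will be reported as campaign success.* The bias can run in either direction. The Introduction's expectation of waning motivation points towards hiding a benefit.
- *That baseline answers of later registrants could act as a concurrent control.* The campaign is territory-wide and registration may follow exposure, so these people are neither unexposed nor comparable in how they selected themselves.

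**Conclusion.** The concern holds in a limited form. Study 3 fixes an uncontrolled pre-post comparison in self-selected registrants and labels the change as intervention effectiveness, while the same article expects the outcomes to move for other reasons. Campaign effect and background change cannot be separated, in either direction, and a baseline that may follow exposure blurs the contrast further.

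On the stated N, alpha and correlation, the chance that background change alone is declared significant runs from about 2–3% at 0.05 SD, through 10–17% at 0.10 SD, to 64–83% at 0.20 SD. These figures rest on assumed shifts, a two-sided test, complete data and pairwise contrasts. They illustrate the problem and do not predict what will happen. Nothing here shows that 515 is wrong or that the analysis model is misspecified. What needs to change is the claim.

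**What to change.** In section 9.2.2, in both the study design and the data and analysis paragraphs, replace the aim of assessing intervention effectiveness with estimating change over time among campaign registrants. Describe d = 0.2 in the power statement as a change over time and not as an intervention effect. State that change will not be attributed to the campaign, and that T0 may follow exposure to advertising.

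Record the date of every survey. Add a GEE sensitivity analysis with reported cases and the restriction level in force at the survey date. Note its limit: if T1 to T5 are common calendar dates, each covariate takes one value per follow-up, so the adjustment can only partly separate epidemic time from campaign time. Do not use the T0 responses of new registrants as a concurrent control.

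The cost is a few sentences, public case and policy data, a little extra analysis and a more modest conclusion.

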### 10.1. Aims

Our proposed study will aim to develop and evaluate the effectiveness of a Web-based psychoeducation programme to address COVID-19 vaccine hesitancy, ‘AI-driven Vaccine Communicator’ (including educational materials, animations of vaccine research and development, and an MI communication skills-based AI, digital assistant). Specifically, we will address three objectives in sequential stages.

Objective 1. To gain an in-depth understanding of the public’s perceptions of/concerns regarding COVID-19 vaccines across different ethnic and socio-economic groups, and develop the Web-based psychoeducation programme ‘AI-driven Vaccine Communicator’.

Objective 2. To conduct a randomised controlled trial to test the effectiveness of the ‘AI-driven Vaccine Communicator’ among members of HK’s population who are hesitant about COVID-19 vaccines.

Objective 3. To perform a pragmatic service evaluation of the ‘AI-driven Vaccine Communicator’ and its long-term significance in response to future mutations of the virus causing COVID-19 and the expansion of the vaccination priority groups.

Our goal is to standardise our intervention so that it can serve as an effective toolkit for clinicians/healthcare providers to increase HK residents’ motivation to vaccinate and to ensure that the programme can be adapted to viral mutations and newly developed vaccines in the medium/long term. The project will involve the active participation of the community, including the development, evaluation, and promotion of our intervention programme as guided by the CBPR approach.

### 10.2. Plan of Investigation

#### 10.2.1. Subjects

Our target population will be Hong Kong residents aged ≥18 who show hesitancy toward COVID-19 vaccines. Participants will be defined as COVID-19 vaccine-hesitant if they have no plan for a date to receive the available COVID-19 vaccines in either 1st, 2nd, or 3rd dose [19], or completed three doses of COVID-19 vaccines not based on their willingness and are hesitant for a future 4th dose or regular vaccines).

#### 10.2.2. Study Methods

Our study will be conducted in three stages. In Stage 1, we will perform an exploratory sequential mixed-methods study with an online survey followed by an exploratory qualitative study. In Stage 2, we will conduct an RCT to test the efficacy of the ‘AI-driven Vaccine Communicator’ relative to being self-informed about COVID-19 vaccines. In Stage 3, after the RCT (Stage 2), we will adopt and implement the intervention as a service evaluation to a wider HK population.

#### 10.2.3. Study design

Stage 1: HK residents of any ethnic and socio-economic background, who are at least 18 years of age and without difficulties in understanding the online survey, will be eligible to be participants. It is estimated that more than 20% of the population will show hesitancy toward COVID-19 vaccines [3]. The minimum sample size for a representative sample is calculated to be 1200, assuming a power of 80% at a confidence level of 95%. A population-based telephone survey will be conducted by randomly selecting the telephone numbers listed in the up-to-date telephone directories of HK residents. This will be conducted by external services provided by local companies. After the completion of the survey, 15–20 respondents will be selected using stratified sampling to achieve a representative sample with respect to age, gender, cultural/ethnic background, and economic background. These participants will be invited to attend an online in-depth qualitative interview to explore their reasons for vaccine hesitancy and thoughts/concerns in relation to COVID-19 vaccines. More participants will be recruited in this way until data saturation is reached. The findings from this mixed-methods study will provide valuable information for the development of the ‘AI-driven Vaccine Communicator’ and enable us to ascertain the extent of hesitancy.

Development of the ‘AI-driven Vaccine Communicator’. The development of the psychoeducation programme will be guided by the Vaccine Hesitancy Determinants Matrix Model (which incorporates vaccination-specific, individual/group, and contextual influences on attitudes towards vaccines) and will integrate MI skills. In addition, educational information regarding the individual, group, and contextual aspects of vaccine hesitancy will be provided on the Web-based intervention platform. The materials on our Web-based platform will be available in multiple formats, including text, videos, and animations, explaining (a) how the vaccine works against COVID-19 and (b) the process of research and development of COVID-19 vaccines and how their safety is ensured. Importantly, we will design a human–computer interaction system, the AI Digital Assistant with MI skills (available in Mandarin, Cantonese, and English), using artificial intelligence-based natural language processing technology. After the initial development of the ‘AI-driven Vaccine Communicator’, the programme content will be validated by a panel of experts in infection control, vaccine science, and MI-based psychosocial interventions. A small-scale pilot test with 8–10 participants will be performed to test the initial feasibility of the programme and gather valuable feedback for improving the content. We will continue to refine the system whenever new information or ideas emerge regarding any questions/concerns in relation to COVID-19 vaccines from our study participants.

Stage 2: Participants of stage 2 will be identified from the survey population of study 1. All Hong Kong-resident adults with COVID-19 vaccine hesitancy will be eligible. People with self-reported cognitive impairments or mental disorders that might interfere with their understanding of the intervention content, and those currently engaged in another clinical trial in relation to COVID-19 vaccines, will be excluded. We calculated our sample based on sample size determination methods for repeated measures. Assuming a Type I error rate of 0.05, primary hypothesis of time x intervention interaction, a change of 1.0 as minimum difference in the mean values of the variable, and estimated correlations among repeated measure of the variable as 0.6 for T0–T1, 0.5 for T0–T2, 0.4 for T0–T3, and a statistical power of 80%, as well as 20% attrition rate, the sample size is calculated to be 168 (i.e., 84 for each group) for two study groups. Block randomisation with a size of 6 will be performed with a computer-generated list of numbers known only to an independent administrator.

Stage 3: The ‘AI-driven Vaccine Communicator’ will be disseminated through collaborating clinicians, NGOs, community centres, and public/private healthcare providers (e.g., GPs). The five main components of the service evaluation assessment will include (1) reach—the proportion of approached participants expressing hesitancy towards COVID-19 vaccines and engaging with the programme throughout the study; (2) adoption—the proportion of participants adopting/completing the Web-based psychoeducation programme; (3) effectiveness—average outcome scores and consistent improvement in vaccine hesitancy outcomes; (4) implementation—the consistency of delivery of the programme, and effect of adaptations made to the implementation process and cost of the delivery; and (5) maintenance—the intention of the research team and participants to continue or adapt the intervention. All relevant community-based/clinical parties will be encouraged to apply our programme in their usual practice and work, our research team will trace all feedback from participants and all participants will be contacted again at 3-month intervals to assess their perceptions of and actions pertaining to COVID-19 vaccination. Stage three (the service evaluation) will consider the practical implementation of our intervention to a wider population, including its reach. Therefore, we will not limit the number of participants for stage 3 because one of the important outcomes is to ascertain how many people access and use it over the evaluation period. The estimate of minimum participant numbers for stage 3 is based on practical issues rather than statistical power to detect significant differences.

